### Evaluation of erythrocyte membrane DHA levels

To evaluate the effectiveness of the diet supplement, a venous blood sample will be taken from half of the study participants with the purpose of finding the DHA concentration in the erythrocyte membranes. Two samples of 2 cc of venous blood will be taken from all participants before taking placebo or DHA, at the 20th or 28th week after recruitment, and at the 37th to 38th week of pregnancy. The blood samples will be taken with a specific kit provided by Lipinutragen-CNR (Bologna, Italy) and shipped to the Lipinutragen-CNR laboratory for testing. The DHA concentration, with respect to the total erythrocyte membrane phospholipids, will be determined by treating a 0.5 ml portion of the maternal blood sample or cord blood samples to separate the erythrocytes and isolate the erythrocyte membranes [24]. The fraction of total phospholipids will be treated with 0.5 M KOH/MeOH for 10 minutes at room temperature in order to obtain the chemical derivation of the phospholipids and compare them with the corresponding chemical fatty acid methyl esters (FAME). FAMEs will be evaluated by gas chromatography (GC) with a flame ionization detector (Agilent 6850; Agilent Technologies, Santa Clara, CA, USA) and a DB-23 column (90% biscyanopropyl/10% phenylcyanopropyl polysiloxane capillary column; 60 m, 0.25 mm ID, 0.25 μm film thickness) or similar, with hydrogen as carrier gas at a constant flow of 1 ml/min; the oven programme will be fixed for the efficient separation of the FAMEs, including the cis and trans isomers. FAMEs can be recognized by comparing them with commercially available references. Trans geometric isomers will be recognized by comparison with a library of trans isomers obtained by radical isomerization as described in previous publications [25]. The FAMEs will be identified by a randomized analysis of the samples by GC coupled with mass spectrometry. The values of the fatty acids will be given as a percentage of all the most important peaks resulting from the GC analysis, representing 98 to 99% of the total chromatographic peaks. The analyses will be repeated so that the value of the DHA can be checked at zero time and compared with the known normal range in healthy subjects.

The statistical assessment of the treatment effectiveness will be obtained by comparison with the DHA values obtained after therapy.

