*In vitro* experiments showed that the viability of the HSCs, deriving from UCB, could be augmented with favourable effects on the engraftment potential [8,9]. These studies revealed that the beneficial effect of the *in vitro* generation of megakaryocytes from UCB, together with a higher ability to survive the cryopreservation, were observed when docosahexaenoic acid (DHA) and arachidonic acid (AA) were supplemented in the growth medium [8,9], increasing the clinical utility of the UCB [9]. In particular, DHA, which belongs to the polyunsaturated fatty acids (PUFAs) family, is a fundamental element of cell membranes [10,11], especially those of the brain and retina [12]. The chemical structure of DHA is illustrated in Figure 1. DHA accumulation in the brain and retina occurs mainly between the last intrauterine trimester and the initial months of life. The metabolic demand of DHA increases progressively in the course of pregnancy, particularly during the third trimester. In this phase a sudden acceleration of foetal growth is observed together with a great deposition of fatty acids in the central nervous system [13]. Therefore, the level of DHA during pregnancy can directly influence the stages of development [14]. Observational studies have also demonstrated a close association between the DHA availability during the perinatal period with long-term cognitive and visual development [15,16]. Besides, the consumption of large quantities of fish, rich in DHA, has been associated with an increase in gestational age, a greater foetal weight at birth and less incidence of pre-eclampsia [17,18].

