**Figure 1 F1:**
[figure not shown]
Chemical structure of docosahexaenoic acid (DHA).

The effect of DHA on foetal weight and development is linked to its effect on the endothelium. DHA increases the flow of blood through vasodilatation in young adults and improves membrane receptor activity. Therefore, it is possible that these fatty acids improve foetal growth, increasing the placental flow by potentiating the activity of prostacyclin versus thromboxane and reducing blood viscosity [19].

Furthermore, treatment with DHA in the third trimester of the pregnancy improves the mother’s DHA status, as indicated by the composition of fatty acids in the maternal erythrocyte membrane [20-22].

However, it should be considered that, during the course of the third trimester, the foetus absorption of DHA is 70 to 100 mg from the maternal bloodstream daily; at the same time, during the second half of the pregnancy, the mother’s needs of DHA supplementation also grows to support the higher request from the foetus without any detrimental effect on her own reserves. Hence, during the third trimester, with an excess or greater availability of DHA, the foetus will tend to accumulate it preferentially in the brain tissue competing with the accumulation on the surface of other cells, specifically, HSCs.

In Denburg *et al*. [23], the effects of a supplementation with n-3 PUFA were assessed in a population of neonatal CD34+ cells as a method for preventing allergies. In this study, the pregnant women were treated, from the 20th week of gestation until delivery, with fish oil capsules or a placebo of olive oil capsules in a randomized control trial (RCT). The results revealed that, in the group given fish oil, the percentage of CD34+ present in the cord blood was greater than that found in the control group (0.879 ± 0.096 versus 0.533 ± 0.041; *P* <0.002) [23]. The study confirmed that a maternal dietary supplementation with n-3-PUFA increases the levels of these fatty acids in the infant’s cell membranes and this has a significant effect on the CD34+ cell population in the cord blood.

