### Statistical analysis

The statistical analysis of the data obtained will be carried out with the aid of the Statistical Package for the Social Sciences (SPSS) program (IBM Corporation, Armonk, NY, USA) in cooperation with the Fatebenefratelli Association for Research (AFaR) of the San Giovanni Calibita Fatebenefratelli Hospital (Rome, Italy). Each experimental group will be compared versus the respective placebo group. The effectiveness of the DHA supplementation at different stages of gestation will also be evaluated by comparing the two experimental groups. The differences between the quantitative variables of the two groups will be analyzed with the Student’s *t*-test and analysis of variance (ANOVA); results of *P* <0.05 will be considered statistically significant. The Spearman test will also be used to compare the parameters of interest, and other quantitative and non-quantitative variables presented by the groups studied.

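### The rule for judging the supplement on erythrocyte DHA reads as before versus after, names no placebo comparator, and is not tied to the planned between-arm comparison

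*Protocol article*

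**What the plan says.** The section Evaluation of erythrocyte membrane DHA levels (Protocol article, Methods) sets out to measure whether the supplement works. Its elements are:

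- **Timing.** Maternal blood is drawn "before taking placebo or DHA, at the 20th or 28th week after recruitment, and at the 37th to 38th week of pregnancy". The legend of Figure 2 gives the same schedule for all participants, so placebo women are sampled too.
- **Reference.** Analyses are repeated so that "the value of the DHA can be checked at zero time and compared with the known normal range in healthy subjects".
- **Rule.** The section then ends: "The statistical assessment of the treatment effectiveness will be obtained by comparison with the DHA values obtained after therapy".
- **Who is sampled.** One sentence says "a venous blood sample will be taken from half of the study participants"; the next says that all participants are sampled.

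The Background states that "The metabolic demand of DHA increases progressively in the course of pregnancy, particularly during the third trimester" and that in the third trimester "the foetus absorption of DHA is 70 to 100 mg from the maternal bloodstream daily".

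The Statistical analysis section gives a general rule: "Each experimental group will be compared versus the respective placebo group". Quantitative variables are tested by Student's t-test and ANOVA, and "results of *P* <0.05 will be considered statistically significant". That section mentions neither erythrocyte DHA nor the pre-treatment value. Cord blood erythrocyte DHA is also measured (Collection of cord blood).

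**The concern.** The rule mentions three things: the value at zero time, an external normal range, and the value after therapy. Placebo is not among them. Followed as it most naturally reads, the analyst would test change from baseline in treated women and call a significant rise evidence of effectiveness.

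Such a test cannot separate the supplement from the passage of gestation. On the article's own account, the second sample falls when foetal demand is high. A shift common to both arms would be credited to the supplement if upward, or would offset a real benefit if downward. Because the interval between samples differs by cohort, the shift may differ too, so before-after changes could not be compared across start weeks. A normal range from healthy subjects does not correct for any of this.

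At stake is the statement that the supplement raised maternal DHA. The reading of the cord-cell results leans on it: without a sound exposure contrast, a null cell result could mean either no biological effect or no rise in DHA.

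**Working it through.** The article gives no sample size, SD, drift or pre-post correlation for erythrocyte DHA, so there is no figure to reproduce. The calculations below illustrate size on assumed inputs.

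**1. Interval between samples**, taking the stated weeks as weeks of gestation:
- week-20 cohort: 37 − 20 = 17 to 38 − 20 = 18 weeks
- week-28 cohort: 37 − 28 = 9 to 38 − 28 = 10 weeks

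**2. Before-after test with no supplement effect.** Paired t-test, two-sided 5% (sidedness is not stated; assumed). Let d be the gestational drift in SDs of the change. The rejection probability comes from the noncentral t with n − 1 degrees of freedom and noncentrality d√n.

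| n in the group (assumed) | critical t | d = 0.3: d√n, rejection | d = 0.5: d√n, rejection |
|---|---|---|---|
| 20 | 2.093 | 1.342, 25% | 2.236, 56% |
| 40 | 2.023 | 1.897, 46% | 3.162, 87% |

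These rejections follow the direction of the drift. They look like benefit only if DHA drifts upward. If it drifts downward they are significant falls.

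**3. The masking case.** Suppose the supplement truly raises DHA by 0.5 SD of the change and gestation lowers it by 0.3 SD. The net change is 0.5 − 0.3 = 0.2 SD. At n = 40 the noncentrality is 0.2 × √40 = 1.265, and power falls from 87% to 23%. At n = 20 it is 0.2 × √20 = 0.894, and power falls from 56% to about 13%.

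**4. The between-arm alternative.** Drift common to both arms cancels in the DHA-minus-placebo difference. A simulation of baseline-adjusted ANCOVA with no supplement effect (50 per arm, pre-post correlation r = 0.5, 4000 runs) rejected in 4.8% of runs at drift 0.3 SD and 4.6% at 0.5 SD, close to the nominal 5%.

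**5. What baseline adjustment adds.** Relative to comparing week 37-38 values alone, ANCOVA multiplies the variance by 1 − r²:
- r = 0.5: 1 − 0.25 = 0.75
- r = 0.8: 1 − 0.64 = 0.36

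For a 0.5 SD difference at 80% power and two-sided 5%, the number per arm at r = 0.5 is 63 with post-treatment values only, 63 with change scores and 48 with ANCOVA. At r = 0.3 the three figures are 63, 88 and 58; at r = 0.7 they are 63, 38 and 33.

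**The case against.** The strongest reply is that the article already plans the right comparison. The Statistical analysis section promises each DHA group against its placebo group for quantitative variables. Erythrocyte DHA is one, and placebo women are bled on the same schedule. The sentence at issue is elliptical: it does not say paired, within-woman or change, and it names no test. A reader might infer that the randomised control is discarded for this measure. The documents do not support that. What stands is that a specific rule and a general rule sit in different sections with nothing linking them, and that the specific one omits placebo.

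A second reply is that the drift is conjecture. This is fair. The Background speaks of demand and foetal uptake, not of a measured change in maternal erythrocyte DHA. If anything, a growing foetal draw suggests a fall, which makes masking more plausible than false benefit. Neither size nor direction can be asserted.

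Third, a reader might infer that baseline adjustment is required for validity. It is not: under randomisation an unadjusted between-arm comparison is valid, and adjustment buys precision. Covariate choice for a supporting biomarker can reasonably be left to an analysis plan. The point here rests on the rule the article does state.

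Finally, maternal DHA is not the sole exposure measure, since cord erythrocyte DHA is measured as well. Cord blood has no pre-treatment value of its own, so a before-after rule could not apply to it.

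**Conclusion.** The point holds in a limited form. The stated rule for supplement effectiveness on erythrocyte DHA most naturally means baseline against post-treatment, names no placebo comparator, and is not connected to the between-arm rule elsewhere in the article. Before-after is an inference from the adjoining sentence, though a strong one. If it were followed, gestational change and supplement effect could not be told apart.

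The size depends on inputs that the documents do not give. At an assumed drift of 0.3-0.5 SD of the change and 20-40 women per group, a paired test with no supplement effect is significant in about 25-87% of trials. A downward drift of 0.3 SD would cut power for a 0.5 SD rise from 87% to 23% at n = 40. With smaller drift the problem shrinks, and with none it disappears.

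The measure supports interpretation and is not the trial's stated aim, which concerns cord-blood cell quantity and viability. The correction should still be made, because it removes an avoidable ambiguity at almost no cost.

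**What to change.** Replace the closing sentence of the erythrocyte DHA section with wording such as: *Week 37-38 maternal erythrocyte DHA will be compared between DHA and placebo within each start-week cohort by ANCOVA, adjusting for the pre-treatment value (or in one model with start-week cohort and a treatment-by-cohort term). Within-arm change will be reported descriptively only.*

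The separate cohort estimates, or the interaction term, should be kept. A single pooled effect with start week only as a covariate would drop the cohort-specific comparisons that the Statistical analysis section plans and would average over 17-18 and 9-10 weeks of supplementation.

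Compare cord erythrocyte DHA between arms in the same way, with the maternal pre-treatment value as covariate. This also gives an exposure measure for women who deliver before the second maternal sample.

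Reconcile the two statements on whether half or all of the participants are sampled, since this sets the n. If it is half, say how they are chosen.

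Cost: wording only for the analysis, because both maternal samples and the cord sample are already planned. Cohort-specific estimates are less precise than a pooled one, and baseline adjustment recovers part of that. The number of women contributing cannot be stated until the sampling conflict is settled.

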### Separation of CD34+ protocol

UCB cells will be stained with fluorescein isothiocyanate (FITC)-conjugated monoclonal antibody against CD45+ and phycoerythrin (PE)-conjugated monoclonal antibody against CD34+. These will be used to identify leukocytes and HSCs, respectively. For analysis of the viability of the cells, they will also be stained with 7-aminoactinomycin D (7-AAD), which will bind to the DNA of cells that are undergoing or have undergone apoptosis (Stem Kit™ Beckman Coulter, Brea, CA, USA). The stained cells will then be lysed (1:10 dilution of ammonium chloride 10x concentrated and deionized water) and analyzed by flow cytometer with a FC 500 cytometer (Beckman Coulter) using CXP software under a single ISHAGE gating strategy.

### Collection of cord blood

Before extracting the cord blood, the recruited pregnant women must carry out serological tests to prove the absence of the following infectious diseases: hepatitis B virus; hepatitis C virus; HIV; cytomegalovirus; human T-cell lymphotropic virus; and syphilis. The report will then be presented to the hospital to obtain the licence.

All the participants will receive a free cord blood collection kit provided by SmartBank (SmartBank, Rome, Italy). Hospital staff assisting the birth will immediately extract and collect the cord blood with the kit. Samples will be shipped to the Biovault technical laboratory (Plymouth, UK) for specific analysis of: volume (ml); pH; cell viability (%); number of CD34+ cells; number of leukocytes; and bacterial and viral tests. In order to determine the DHA percentage in the cord blood erythrocyte membranes, 2 cc of the extracted cord blood will be sent to the Lipinutragen-CNR laboratory in Bologna.

### Processing of cord blood

The cord blood processing procedures will be carried out in the Biovault laboratory in the UK, possessing medical and healthcare products, and regulatory agency registration, operating according to the World Health Organization (WHO) international good manufacturing practices protocol, and the International Organization for Standardization (ISO) ISO 9001:2008 and ISO 13485:2012 standards, and aseptic treatment, grade A certificate, will be performed in a Biosafety Level 3 (BSL-3) clean room. Biovault is accredited by the American National Standards Institute (ANSI) regulatory accrediting body, Advancing Transfusion and Cellular Therapies Worldwide, and the Joint Accreditation Committee of the International Society for Cellular Therapy (ISCT) and the European Group for Blood and Marrow Transplantation (EBMT) (JACIE), and has a Human Tissue Authority licence.

The sample will enter the BSL-3 clean room through a hermetically sealed window with positive outlet atmospheric pressure. Inside the BSL-3 clean room the sample will be weighed, centrifuged, measured volumetrically, and subjected to microbiological tests, flow cytometry analysis and phase separation with subsequent selection of mononuclear cells. The sample containing the cells will be inserted into the final Pall container (Pall Corporation, Port Washington, NY, USA) and mixed at 4°C with 10% dimethyl sulfoxide (DMSO). The bag or Pall, with a unique, indelible identification code, will be inserted into a computerized temperature reduction system. After the temperature is reduced, the Pall will be inserted in a sealed metal container and preserved in liquid nitrogen vapour at -196°C.

### Flow cytometry

The flow cytometry analysis will be carried out within 48 hours of the UCB sample collection with a FC 500 flow cytometer (Beckman Coulter) on ISHAGE software platform. The analysis method uses double fluorescence (FITC-PE) with rat monoclonal antibody. For a simultaneous identification and count of the CD45+ and CD45+ CD34+ cells, a double antibody marking will be carried out, evaluating the percentage of the positive population with regards to the absolute count. The CD34+ receptor will be used as an indicator of the total number of progenitor stem cells of the haematopoietic lineage. The cell viability will be evaluated by flow cytometry using 7-AAD (Invitrogen Life Technologies, Carlsbad, CA, USA). Apoptotic, necrotic and metabolically inactive cells will be stained and thus considered non-viable while viable cells remain unstained. Total cells will be counted by flow cytometry discriminating between non-viable (7-AAD positive cells) and viable cells (7-AAD negative cells). The flow cytometer will be calibrated every 24 hours and quality controls performed according to the UK National External Quality Assessment Service (NEQAS) protocol.

### Statistical analysis

The statistical analysis of the data obtained will be carried out with the aid of the Statistical Package for the Social Sciences (SPSS) program (IBM Corporation, Armonk, NY, USA) in cooperation with the Fatebenefratelli Association for Research (AFaR) of the San Giovanni Calibita Fatebenefratelli Hospital (Rome, Italy). Each experimental group will be compared versus the respective placebo group. The effectiveness of the DHA supplementation at different stages of gestation will also be evaluated by comparing the two experimental groups. The differences between the quantitative variables of the two groups will be analyzed with the Student’s *t*-test and analysis of variance (ANOVA); results of *P* <0.05 will be considered statistically significant. The Spearman test will also be used to compare the parameters of interest, and other quantitative and non-quantitative variables presented by the groups studied.

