## Methods

### Recruitment

The trial is designed to target pregnant women within the 20th or 28th week of gestation. At the time of recruitment, the participants will sign an informed consent form, and complete a questionnaire authorizing third parties to obtain demographic, anamnestic and nutritional data. The information thus obtained will be entered into a case report form for each pregnant woman.

Detailed information on benefits and risks of DHA will be provided to study candidates. Participants that meet pre-specified eligibility criteria (Table 1) and provide written informed consent will be enrolled in the study.

**Table 1 T1:** Eligibility criteria

**Inclusion criteria**	**Exclusion criteria**
Caucasian	When it is impossible to collect cord blood (bureaucratic reasons or because of emergencies regarding the health of the mother or the baby)
Non-smokers	Women who have taken other supplements containing DHA or fish oil
Over 18 years of age	Mother with a temperature of 39°C during delivery
Single pregnancy	UCB samples with a volume of less than 80 ml and/or less than 70% cell vitality
Absence of diabetes or hypertension, or any other type of pathology requiring pharmacological therapy	
Absence of chromosome abnormalities and/or congenital malformations in the foetus	
HBV, HCV, HIV and CMV negative	

CMV, cytomegalovirus; DHA, docosahexaenoic acid; HBV, hepatitis B virus; HCV, hepatitis C virus; UCB, umbilical cord blood.

The Ethics Committee of the San Giovanni Calibita Fatebenefratelli Hospital (Rome, Italy), in compliance with the Helsinki Declaration, approved the study protocol (9 July 2009, reference: 35/2009; and 9 December 2010, reference: 67/2010). The trial is registered at the International Standard Randomised Controlled Trial Number Register (ISRCTN58396079).

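### Cord-blood cell outcomes are to be compared without baseline adjustment although diet and pre-treatment DHA are collected; the comparison is valid, but precision of unknown and probably modest size is given up

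*Protocol article*

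**What the plan says.** All places are in the Protocol article.

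- **Statistical analysis.** "The differences between the quantitative variables of the two groups will be analyzed with" Student's t-test and ANOVA, with P "<0.05 will be considered statistically significant". The planned contrasts are separate by start week: "Each experimental group will be compared versus the respective placebo group". The two DHA groups (week 20 and week 28) are also compared with each other. The only stated use of further variables is this: "The Spearman test will also be used to compare the parameters of interest, and other quantitative and non-quantitative variables presented by the groups studied".
- **Recruitment.** Each woman completes a questionnaire so that "demographic, anamnestic and nutritional data" can be entered in her case report form.
- **Evaluation of erythrocyte membrane DHA levels.** "Two samples of 2 cc of venous blood will be taken from all participants before taking placebo or DHA". The sentence just before it limits the venous sampling to half of the women. The Abstract and the caption of Figure 2 say all.
- **Background.** A cited randomised trial of maternal n-3 supplements is summarised as showing that a rise in these fatty acids occurs in the infant's cell membranes and that "this has a significant effect on the CD34+ cell population in the cord blood". The trial's own hypothesis is that DHA supplementation raises the metabolic activity of cord-blood stem cells.
- **Flow cytometry.** Analysis takes place "within 48 hours of the UCB sample collection". The article does not say that the elapsed hours are recorded.

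**The concern.** If supplementary DHA changes cord-blood cells, the DHA a woman already gets from food may do so too. Table 1 excludes women who have taken DHA or fish-oil supplements but not women who eat fish, so some dietary variation remains. A t-test leaves any outcome variation due to diet in the error term. A Spearman correlation between diet and outcome describes that relation but does not remove it from the treatment comparison.

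At stake are the width of the confidence interval and the power for the cell outcomes. A chance imbalance between arms in fish intake would also go unaccounted for in the estimate. The point concerns the cell outcomes, not the comparison of erythrocyte DHA before and after treatment.

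**Working it through.** The article states no sample size, power, target difference, SD or correlation, so there is no figure to reproduce. Everything below is illustrative. It assumes a two-sided 5% test (the article does not state sidedness), equal arms and the normal approximation. Arm sizes are per arm within one start-week cohort.

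**1. Gain as a function of the correlation ρ between baseline covariate and outcome.** The adjusted SE equals the unadjusted SE × √(1 − ρ²). The table takes a comparison sized for 80% power unadjusted at a standardised effect of 0.5 (63 per arm).

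| ρ (assumed) | R² = ρ² | Fall in SE | Power at 63 per arm | n per arm for 80% power |
|---|---|---|---|---|
| 0.1 | 0.01 | 0.5% | 80.5% | 63 |
| 0.3 | 0.09 | 4.6% | 83.7% | 58 |
| 0.5 | 0.25 | 13.4% | 90.0% | 48 |
| 0.7 | 0.49 | 28.6% | 97.6% | 33 |

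**2. Where R² might lie.** Assume a linear dose-response, an effect of δ SD for 250 mg/day, and background intake with SD s mg/day. Then R² = (δ × s/250)².

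- Low end, δ = 0.3, s = 75: (0.3 × 75/250)² = 0.09² = 0.8%.
- Central, δ = 0.5, s = 150: (0.5 × 150/250)² = 0.3² = 9%. With questionnaire reliability 0.5, this is 4.5%.
- High end, δ = 0.8, s = 200: (0.8 × 200/250)² = 0.64² = 41%.

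**3. Power in the central case.** With 64 per arm and δ = 0.5, δ/SE = 0.5/√(2/64) = 2.828.

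- Unadjusted: Φ(2.828 − 1.960) = 80.7%.
- R² = 0.045: Φ(2.828/√0.955 − 1.960) = Φ(0.934) = 82.5%.
- R² = 0.09: Φ(2.828/√0.91 − 1.960) = Φ(1.005) = 84.3%.

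As equivalent sample size, 1/(1 − R²) is 1.047 to 1.099, that is about 5% to 10% more women.

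**4. Cost if the covariate is useless.** With p covariates and N women in total, the variance is multiplied by about 1 + p/(N − p − 3).

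- 10 per arm, p = 1: 1 + 1/16 = 1.06.
- 50 per arm, p = 1: 1 + 1/96 = 1.01.
- Three covariates: 1.21 at 10 per arm and 1.03 at 50 per arm.

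At 10 per arm the lower central case would not pay: 0.955 × 1.0625 = 1.015. At 50 per arm it would: 0.955 × 1.0104 = 0.965.

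**5. If erythrocyte DHA is measured in a random half only.** Analysing only women with a value multiplies the variance by 2(1 − ρ²). Keeping all women, with missing baseline values set to the mean, multiplies it by about 1 − ρ²/2.

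| ρ | Complete-case variance ratio | Mean-imputed variance ratio | Fall in SE, mean-imputed |
|---|---|---|---|
| 0.1 | 1.98 | 0.995 | 0.3% |
| 0.3 | 1.82 | 0.955 | 2.3% |
| 0.5 | 1.50 | 0.875 | 6.5% |
| 0.7 | 1.02 | 0.755 | 13.1% |

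Complete-case adjustment is worse than no adjustment at every ρ shown.

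**The case against.** **No error is shown.** An unadjusted comparison of randomised arms is valid, and articles often leave covariate lists to a fuller plan that is not available here. The first part stands in full. The second stands in part: an unseen plan may add covariates, but the article does name a method, and a better one is available from data it says are collected. That makes this an improvement to a stated choice, not a complaint about missing detail.

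**The gain may be small.** This stands. The assumed ranges run from negligible to large. Two features of the article count against the upper end. Excluding supplement users narrows background intake. The Background section also says that in the third trimester surplus DHA goes preferentially to the brain in competition with stem cells, which weakens a linear dose-response.

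**Prognostic value is inferred.** This also stands. A reader might infer that the trial's hypothesis makes baseline DHA prognostic. The article hypothesises an effect of supplementation; it nowhere says that background DHA predicts cord-blood cells.

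**The covariate may not exist in usable form.** The article mentions nutritional data without describing a fish or DHA score, and it contradicts itself on who gives venous blood. This limits which covariate can be used but does not remove the point.

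**Hours to cytometry.** A reader might want the time from collection to cytometry in the main model as well, on the ground that the 48-hour limit obliges the trial to record it. The article gives the limit but states no recording of times. The variable also arises after randomisation, so adjusting for it assumes that treatment does not affect it. That is plausible under blinding but is still an assumption.

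**Conclusion.** The point holds as a modest efficiency gain. The article fixes unadjusted tests for the cord-blood cell outcomes while collecting pre-treatment measures that may predict them. The absence of a covariate does not bias the randomised DHA-versus-placebo contrasts, and a reader who took it as a flaw in validity would go beyond the documents. Nor is adjustment strictly free, since it costs precision in very small arms or if women without a baseline value are dropped.

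The size cannot be established from the article. The fall in SE is 0.5% to 29% for ρ of 0.1 to 0.7. The central assumption corresponds to about 2 to 4 percentage points of power at 64 per arm. These figures rest on the assumed correlation, a linear effect of intake, and arm sizes the article does not state.

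**What to change.** Revise Statistical analysis as follows. The Trial status section says recruitment is under way, so the model should be fixed before unblinding.

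1. For each cord-blood cell outcome, pre-specify a linear model with treatment arm and one baseline DHA-exposure covariate. Keep the planned contrast within each start-week cohort, by separate models or an arm-by-start-week term. A model with arm and start week but no interaction would replace those contrasts with a single pooled effect.
2. Reconcile the two sentences on venous sampling in Evaluation of erythrocyte membrane DHA levels. If all women are sampled, baseline erythrocyte DHA can be the covariate. If not, use one dietary fish or DHA measure defined in advance from the recruitment questionnaire.
3. Fill missing baseline values by a simple pre-stated imputation, so that no woman is dropped for lack of a covariate.
4. Report adjusted differences with 95% confidence intervals beside the unadjusted t-test.
5. Leave hours from collection to cytometry out of the main model. Use it at most in a sensitivity analysis, if the times are recorded and with the assumption of no treatment effect on them stated.

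The cost is some analysis wording, definition of the dietary measure if it is used, and about one degree of freedom. If the covariate proves useless, the variance rises by roughly 1% at 50 per arm and 6% at 10 per arm.
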